### Proton pump inhibitor

Both groups of patients will receive PPI treatment, one pill at a time, twice a day, orally 30–60 min before meals. PPI will be used as the control treatment method because it has been the most conventional empirical treatment for LPRD [1]. No evidence supports the superiority of one PPI over another for LPRD; therefore, we will use the most commonly used omeprazole. Omeprazole must be taken twice a day, because studies have shown that no PPI can suppress acid (pH > 4 in the stomach) for more than 16 h [28].

### Outcomes

#### Primary outcome

The RSI is a widely used scale for diagnosing and evaluating LPRD. It is a well-established patient self-report questionnaire and is a tool with publicly available data. The RSI scale contains 9 items, which are scored on a 6-point Likert scale (0–5), with a score of 0–45. The higher the score, the more severe the symptoms. RSI > 13 points will be considered possible patients with LPR [29]. RSI remains the “standard” in this field, although it has some shortcomings and limitations [30]. Therefore, we will select it as the primary outcome to assess the severity of reflux. Participants will be evaluated for changes in scale scores before the start of the experiment (after the informed consent will be obtained) and at 4, 12, and 24 weeks of the experiment (Fig. 2). The last of the nine items of the RSI is a complex GORD problem that includes heartburn, chest pain, indigestion, and acid reflux. Patients with dyspepsia may reach 5 points on the ninth item, which may be mistaken for patients with LPR. Referring to the report of a clinical trial, we will require that after the ninth item is removed, the score must be greater than or equal to 10 to be included [31]. Significant improvement will be defined statistically here, when the total score values will decrease by more than 50%. In addition, the valid rate will be defined as the proportion of patients showing significant and effective improvements.

**Fig. 2 Fig2:**
[figure not shown]
Study design

#### Secondary outcomes

The reflux finding score (RFS) is a widely used scale [32]. According to the results of laryngoscopy, it assesses whether there are signs of vocal cord edema, granuloma in the larynx, posterior hyperplasia, mucosal hyperemia, or erythema. The total RFS score ranges from 0 to 29. Patients will be instructed to undergo laryngoscopy before treatment and 4 and 12 weeks after treatment to objectively assess the changes in reflux signs.

### Laryngopharyngeal Reflux-Health-related Quality of Life

Laryngopharyngeal Reflux-Health-related Quality of Life (LPR-HRQL) is a tool specially used to assess the quality of life of patients with throat symptoms, which can effectively and reliably assess the quality of life of patients with LPR [33, 34]. It has a total of 43 items divided into four areas and an overall impact category. The higher the score, the greater the impact of the disease on the patient’s quality of life, and the scale is significantly sensitive to changes [35].

### Visual analog scale for throat pain

RSI lacks an evaluation of throat pain, but throat pain is a common symptom in patients with LPR. Therefore, a VAS will be added to indicate changes in the patients before and after treatment. A score of 0 indicates no throat pain, and a score of 10 indicates extreme throat pain. Patients will be scored according to the severity of their symptoms.

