### Inclusion criteria

 ① Patients aged ≥ 18 years

② Patients with symptoms of globus sensation, continuous throat clearing, hoarseness, pronunciation fatigue, throat pain, chronic cough, and dyspnea for more than 6 weeks

③ Patients with RSI > 13 points and/or RFS > 7 points, with Dx-pH monitoring diagnosed as acid reflux

④ Patients who agree to sign an informed consent form and participate in clinical trials

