#### Statistical analyses

The measurement data that conform to the normal distribution will be represented by the mean ± standard deviation, and the measurement data that do not conform to the normal distribution will be represented by M (P25, P75). The analysis will be performed based on intention-to-treat and will be performed using SPSS version 23.0. A bilateral *P* value of less than 0.05 will be considered significant. Continuous variables will be compared using the t-test or Mann–Whitney *U* test. The chi-squared test or Fisher’s exact test will be used to compare the qualitative data.

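### The throat-pain VAS is compared without baseline adjustment although patients may enter at 0 and cannot then improve; adjusting for baseline VAS recovers power at no cost and keeps all randomised patients

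*Protocol article*

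**What the plan says.** All references are to the protocol article.

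- **The measure.** The section on the visual analog scale gives the reason for the score, "RSI lacks an evaluation of throat pain", and its purpose, with the lower anchor: "a VAS will be added to indicate changes in the patients before and after treatment. A score of 0 indicates no throat pain". Both anchors are: "A score of 0 indicates no throat pain, and a score of 10 indicates extreme throat pain". The Abstract lists change in this score among the secondary outcomes. The Dx-pH monitoring section schedules it at baseline and weeks 4 and 12.
- **How widespread throat pain is.** The same section says only that "throat pain is a common symptom in patients with LPR". No proportion is given.
- **Entry.** Inclusion criterion 2 reads: "Patients with symptoms of globus sensation, continuous throat clearing, hoarseness, pronunciation fatigue, throat pain, chronic cough, and dyspnea for more than 6 weeks". Criterion 3 reads: "Patients with RSI > 13 points and/or RFS > 7 points, with Dx-pH monitoring diagnosed as acid reflux". Exclusion criterion 7 removes patients scoring below 10 on the RSI without its ninth item. No criterion sets a minimum throat-pain score.
- **Analysis.** Under Statistical analyses, the analysis is by intention-to-treat, and "Continuous variables will be compared using the t-test or Mann–Whitney" U test. The section mentions no covariate.
- **Power.** The Sample size section concerns the RSI only. No effect, SD or power is stated for the VAS.

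**The concern.** The lower end of the VAS means no pain, so a patient who enters at 0 can only stay at 0 or get worse. Such patients tell us nothing about relief of throat pain, yet they count fully in an unadjusted comparison of all randomised patients. The primary outcome is protected from this: exclusion criterion 7 ensures at least 10 points on the first eight RSI items, so every patient has room to improve. The VAS has no such safeguard, and the entry scores do not select for throat pain.

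Two things are at stake. The all-patient mean difference depends on how many pain-free patients happen to enrol. The trial could also report no effect on throat pain when patients who had it did benefit. The score was added precisely because the primary scale does not cover this symptom.

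**Working it through.** **The plan's own figure.** There is none for the VAS. For the RSI, the standardised effect is 4.5/6 = 0.75. At two-sided alpha 0.05 and 80% power, the normal formula gives 2 × (1.96 + 0.84)² / 0.75² ≈ 27.9, so 28 per arm. The exact t-test calculation gives 28.9, so 29, as stated. With 10% dropout, 29/0.9 = 32.2, so 33. (This uses 0.05; the printed percent sign is a separate matter.) With 35 per arm and 10% dropout, about 31 per arm are evaluable.

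**Assumed inputs, none of them from the protocol.** Let p be the share with throat pain at baseline. Among these patients the mean VAS fall is 1.5 (control) and 3.0 (TEAS), with SD of change s = 2. The standardised effect is then 1.5/2 = 0.75, the same as for the RSI. Pain-free patients stay at 0.

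**Algebra for the unadjusted change score.**

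- Mean difference in all patients = p × 1.5.
- Variance of change in an arm with mean fall m = p·s² + p(1−p)·m².
- At p = 0.5 the difference is 0.75. The variances are 0.5×4 + 0.25×2.25 = 2.56 (control) and 0.5×4 + 0.25×9 = 4.25 (TEAS).
- Standard error = √((2.56 + 4.25)/31) = 0.469, so z = 0.75/0.469 = 1.60 and power = Φ(1.60 − 1.96) = 36%.
- In patients with pain only, 15.5 per arm: standard error = √(2×4/15.5) = 0.718, z = 1.5/0.718 = 2.09, power 55%.

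The same formulas give, for all patients against patients with pain only, 65% v 75% at p = 0.8, 45% v 63% at p = 0.6 and 21% v 37% at p = 0.3. At p = 1 both are 84%. Total variance need not rise (the control variance here falls from 4 to 2.56). Power is lost because the spread does not shrink in proportion to the difference.

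**Simulation on the bounded scale.** 31 per arm, 4000 runs per setting. In patients with pain, baseline is about 5 (SD 1.5, limited to 1–10). Follow-up is baseline minus 1.5 or 3.0 plus noise with SD 2, limited to 0–10. Power at two-sided 0.05:

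| p | t-test, change, all | Mann–Whitney, change, all | t-test, follow-up score, all | Baseline-adjusted (ANCOVA), all | t-test, change, pain only |
|---|---|---|---|---|---|
| 1.0 | 78% | 76% | 61% | 79% | 78% |
| 0.8 | 59% | 54% | 41% | 68% | 70% |
| 0.6 | 41% | 33% | 26% | 55% | 56% |
| 0.5 | 31% | 24% | 21% | 47% | 48% |
| 0.3 | 18% | 13% | 12% | 29% | 31% |

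**Adjustment or restriction?** A second simulation (32 per arm, noise SD 2) compared the all-patient t-test on change, the all-patient ANCOVA, and ANCOVA restricted to baseline VAS above 0:

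| p | t-test on change, all | ANCOVA, all | ANCOVA, VAS > 0 |
|---|---|---|---|
| 0.3 | 15% | 26% | 28% |
| 0.5 | 26% | 41% | 42% |
| 0.7 | 41% | 59% | 61% |
| 0.9 | 60% | 69% | 70% |

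Adjustment gives nearly all the gain; restriction adds 1 or 2 points. Adjustment restores power, not the size of the estimate: the all-patient mean difference remains roughly p times the effect in patients with pain.

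**The case against.** - **Entry may require throat pain.** Criterion 2 joins its seven symptoms with a conjunction. Read literally, every patient would have throat pain, and also hoarseness, cough, dyspnea and the rest. That reading is implausible and sits badly with the description of throat pain as merely common. Even so, no minimum VAS would follow from it. What stands is that the documents do not show how many patients start at 0, and the wording of criterion 2 should be clarified.
- **Nothing is invalid.** A reader might infer that patients at 0 bias the comparison or inflate false positives. They do not. The all-randomised comparison is properly randomised, its mean difference is a legitimate quantity for the patients enrolled, and patients at 0 can still worsen and so inform on harm. This stands in full.
- **The subgroup should be the main analysis.** A reader might infer this too. The calculations do not support it. Restriction gains almost no power over adjustment, narrows the population, drops new pain from the estimate and departs from the stated intention-to-treat principle.
- **The size is assumed.** True. Every VAS input is a reviewer's assumption. At p = 0.9, with noise SD 1.5, 2.0 and 2.5, another run gave 87% v 92%, 66% v 72% and 51% v 54% for the all-patient t-test against restricted ANCOVA. At high prevalence little is lost.
- **Covariates belong in an analysis plan that is not shown.** This has some force. But the article does name the tests, and for this outcome the named tests are weaker than a readily available alternative.

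**Conclusion.** The point holds as an inexpensive improvement to a secondary analysis. As stated, the throat-pain VAS is compared in all randomised patients without baseline adjustment, although patients may start at a score from which they cannot improve. The consequence is a diluted mean difference and lost power, with no bias and no type I error inflation. The primary RSI analysis is untouched, and the protocol claims no power for the VAS.

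The size is conditional on the unknown share with pain at entry. Under the assumptions above, the unadjusted t-test on change gives up about 16 percentage points of power against the adjusted analysis at a 50% share (31% v 47%) and 9 points at 80% (59% v 68%). If everyone has pain it gives up almost nothing (78% v 79%). Mann–Whitney, or a t-test on the follow-up score alone, does worse whenever pain-free patients are present. The direction was the same in every set of assumptions tried; the exact values differ. All runs hold pain-free patients at 0, so new-onset pain is not modelled.

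**What to change.** In Statistical analyses, state that the throat-pain VAS at week 4 and at week 12 is compared between arms in all randomised patients, with baseline VAS as a covariate (ANCOVA). Add two supportive results:

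1. The same adjusted comparison in patients with baseline VAS above 0, labelled as applying to patients with throat pain at entry. This group is defined by a baseline score, so the comparison remains randomised, and it shows the effect undiluted.
2. By arm, the number of patients with baseline VAS 0 who report throat pain at follow-up, so that worsening is visible.

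Report the number per arm with baseline VAS 0, so that readers can judge the dilution.

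The cost is two or three sentences. Baseline, week 4 and week 12 scores are already scheduled, so no new data, visits or patients are needed. The stated intention-to-treat principle is kept.

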### Dx-pH monitoring

The oropharyngeal pH test is an important test for the objective diagnosis of LPR. Some researchers compared the ability of oropharyngeal and esophageal pH monitoring to predict the response of patients with suspected LPR to PPI treatment, indicating that the oropharyngeal probe has a higher positive predictive power than esophageal measurement [36]. All patients will be required to undergo Dx-pH testing before enrollment to determine whether they have acid, alkaline, or mixed reflux. Only patients with acid reflux will be included. Because PPI has a great effect on acidic and mixed reflux, it can alkalize the gas and liquid of reflux and reduce the activity of pepsin, but it has little effect on alkaline reflux [37]. In previous studies, because of the time and economic cost of pH testing, most patients are unwilling to perform pH monitoring again after treatment. Therefore, we will consider pH detection as a secondary outcome.

All outcomes will be measured at the four time points of the study. Dx-pH monitoring will be performed at baseline and 12 weeks. LPR-HRQL score, throat pain VAS score, and RFS will be assessed at baseline, 4, and 12 weeks. RSI will be evaluated at baseline, and 4, 12, and 24 weeks. The time schedule for the inclusion of participants, intervention, and evaluation is shown in Fig. 3.

**Fig. 3 Fig3:**
[figure not shown]
Schedule of enrolment, intervention, and assessment (SPIRIT) figure

### Adverse events

Adverse events (AEs) will be reported to the data monitoring ethics committee, and experts will classify AEs as treatment-related or non-treatment-related based on their potential association with TEAS or PPI within 24 h after the occurrence. If a severe AE will occur, the participant will be required to withdraw from the trial immediately and seek medical help at the nearest general hospital. There will be no anticipated harm or compensation for trial participation.

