### Quality assurance and quality control

To ensure the quality of the study, otolaryngology experts in Chinese medicine, Western medicine, and statisticians will review and revise the study protocol prior to the start of the experiment. Other standardized procedures for research operations, including details such as filling out questionnaires, recruiting participants, treatment interventions, AE evaluation, and data management, have also developed uniform standards. Any deviations from the protocol will be fully documented using a breach report form. We will update the protocol in the clinical trial registry in the event of protocol modifications. The Project Management Group will meet every 3 months to review the trial conduct. The Clinical Medical Research Ethics Committee of the First Affiliated Hospital of Anhui Medical University will meet every half year to review conduct throughout the trial period. The clinical research assistant will periodically review the data to ensure the authenticity, timeliness, and data quality of the data collection. All data will be collected in the form of paper + electronic questionnaires, finally transferred to an Excel spreadsheet, and stored for at least 5 years after the trial results will be published. Therefore, all data collected during the research process will be kept strictly confidential and used only by researchers. The patient’s private information, including name and phone number, will be strictly protected and will never be allowed to be disclosed. If reviewers or readers have any questions about our published data, they can contact the corresponding author to obtain the data. Researchers will make detailed treatment plan descriptions, acupoint pictures, videos, and TEAS treatment procedures and distribute them to each participant. Researchers will ensure that the participants comply with the intervention plan. A specially established communication team will guide participants in their interventions and will be available to answer their questions. All treatments will be free of charge to participants, and for those who will discontinue or deviate from the intervention protocols, we will keep the data we have collected and record the reasons for quitting. Participants will be registered with a phone number and address for further contact if they miss the follow-up time.

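### The severe-AE rule takes participants out of the trial, not only off treatment, which ends RSI collection for them and conflicts with the stated intention-to-treat analysis

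*Protocol article*

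**What the plan says.** Four statements in the protocol article bear on this point.

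- **Adverse events.** "If a severe AE will occur, the participant will be required to withdraw from the trial immediately". The preceding sentence has experts judge whether each event is related to TEAS or PPI, but the withdrawal rule makes no use of that judgement. It is worded identically for both arms.
- **Quality assurance and quality control.** "for those who will discontinue or deviate from the intervention protocols, we will keep the data we have collected and record the reasons for quitting". The section also says: "Participants will be registered with a phone number and address for further contact if they miss the follow-up time".
- **Dx-pH monitoring (assessment schedule).** "RSI will be evaluated at baseline, and 4, 12, and 24 weeks". The Primary outcome section says of the RSI: "It is a well-established patient self-report questionnaire".
- **Statistical analyses.** "The analysis will be performed based on intention-to-treat and will be performed using SPSS version 23.0".

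**The concern.** An intention-to-treat comparison needs outcomes from everyone randomised, including those who stop treatment early. The article does not distinguish stopping treatment from leaving the trial. Its severe-AE rule imposes the second, and its sentence on discontinuation or deviation speaks of quitting.

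Two things are at stake. First, outcomes that are never collected cannot be recovered at the analysis stage; a method for missing data can only replace them with assumptions. Second, patients with severe events matter for both efficacy and safety, and the trial aims to assess both. Only one arm has the 12-week home TEAS programme, and participants and outcome assessors know the allocation, so departures could be unequal between arms and related to outcome.

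**Working it through.** **Step 1: set the statements side by side.** Take a participant with a severe AE at week 3, unrelated to treatment. Under the Adverse events section this person leaves the trial. The RSI assessments at weeks 4, 12 and 24 are then not made. The Statistical analyses section still counts this person in the randomised arm. Both instructions can be followed only if leaving the trial is read as leaving treatment, which is not what is written. The contact provision does not clearly close the gap, because someone required to leave the trial has no scheduled follow-up to miss. For those who discontinue or deviate without a severe AE, the text is silent on further assessments; it does not rule them out.

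**Step 2: reproduce the plan's sample size.** Inputs from the Sample size section: difference 4.5, SD 6, power 80%, two-sided test. The section prints alpha as 0.05%, but the stated size is reproduced with 0.05, the level given under Statistical analyses; that discrepancy is a separate matter.

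- Normal approximation: n = 2 × (1.96 + 0.84)² × (6/4.5)² ≈ 27.9, so 28 per arm.
- Exact t-test: 28.9, so 29 per arm, as stated.
- Dropout of 10%: 29 / 0.90 = 32.2, so 33 per arm, as stated. The plan recruits 35.

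**Step 3: precision.** t-test power at alpha 0.05:

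| Analysed | Power |
|---|---|
| 35 per arm | 87.1% |
| TEAS arm loses 1 (34 v 35) | 86.6% |
| TEAS arm loses 2 (33 v 35) | 86.1% |
| TEAS arm loses 4 (31 v 35) | 85.0% |
| 29 per arm | 80.1% |

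Loss of power is therefore not the problem; the dropout allowance covers it.

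**Step 4: bias, as an illustration.** Let a fraction f of one arm be missing, and suppose those patients would have scored D points worse on average than the rest of the arm, whose mean is m. The mean for everyone randomised is (1 − f) × m + f × (m + D) = m + f × D, while the observed mean is m. With loss in one arm alone, the comparison of observed scores is off by f × D. With loss in both arms, it is off by the difference between the two products. The article gives neither f nor D, so both are assumptions.

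| Scenario | D = 3 | D = 9 |
|---|---|---|
| Equal f and equal D in both arms | 0 | 0 |
| One patient in one arm only (f = 1/35) | 0.09 | 0.26 |
| 10% in one arm only | 0.3 | 0.9 |

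Against the 4.5-point target, the last row is 0.3/4.5 = 7% to 0.9/4.5 = 20%. The 10% is borrowed from the plan's overall dropout allowance, which is not a rate of severe AEs.

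**The case against.** The strongest reply has four parts.

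1. **Data retention supports intention-to-treat.** Saying that "we will keep the data we have collected and record the reasons for quitting" means that data are not discarded. A reader might infer that early stoppers contribute only what was collected before they stopped, but the text contains no such restriction, and the section provides for contacting people who miss follow-up. This stands. The discontinuation sentence is unclear rather than contradictory; the firm conflict lies in the severe-AE rule.
2. **Selective loss is not shown.** A reader might infer that outcomes will be lost mainly in the TEAS arm and that this flatters TEAS. The rule is the same in both arms, both take a PPI, no AE or dropout rate by arm is given, and the article anticipates no harm. In an open-label trial, control patients with poor relief could also leave, which would push the other way. This stands too.
3. **Missing-data methods belong in the analysis plan.** A reader might infer that the result will be a comparison of completers labelled intention-to-treat. The article does not say how missing scores are handled, and such detail is commonly left to a fuller document that is not shown here. That inference is therefore not supported. The objection does not remove the point, however: an analysis plan can choose a method, but it cannot restore assessments that the protocol has ended.
4. **Safety follow-up is not expressly ended.** The article requires AE reporting and classification and directs the patient to medical care. It does not say that AE recording stops at withdrawal. This is fair, though it does not say that recording continues after a participant has left.

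**Conclusion.** The point holds in a limited form. As written, the severe-AE rule ends RSI collection for the patients it reaches and is inconsistent with the stated intention-to-treat analysis. The handling of others who discontinue or deviate leaves open whether their remaining assessments take place.

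The number affected is not given and may be very small, possibly zero. Unequal loss between arms is plausible because only one arm receives TEAS and allocation is known, but its size and direction are not established. The illustrated bias runs from 0 with balanced loss to about 0.3 to 0.9 RSI points with 10% loss in one arm alone and an assumed deficit of 3 to 9 points. These figures show what informative loss could do. They do not measure the effect of the severe-AE rule, and the shift could favour either arm. The correction is worth making because it is cheap and because the missing scores could not be recovered later.

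**What to change.** Reconcile the Adverse events, Quality assurance and quality control, and Statistical analyses sections, leaving every clinical rule on when treatment stops as it is:

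- Define stopping study treatment and withdrawing from the trial as separate events, and reserve the second for participants who decline further follow-up.
- State that every randomised participant who still consents is followed for RSI and AEs at weeks 4, 12 and 24, by phone or electronic form if needed, whether or not treatment has stopped.
- State that these participants are analysed in the arm to which they were randomised.
- Record the date and reason for each event by arm, so that the extent and balance of any loss can be reported.

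The cost is protocol wording and a few extra contacts. The RSI is self-reported, electronic questionnaires are already in use, and phone numbers and addresses are already held.
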